### Ethics Approval

The study protocol was approved by the USF institutional review board (STUDY007451). Informed consent to participate in the study will be obtained from each participant in the intervention cohort. A waiver of informed consent was obtained for participants in the control group as it is not feasible to obtain since participants may no longer establish care at USF. In addition, the electronic health record may have unreliable or inaccurate contact information for the participants, or the participant may be deceased.

All data will be stored in REDCap (Research Electronic Data Capture, Vanderbilt University), a web-based HIPAA (Health Insurance Portability and Accountability Act)-compliant platform hosted at USF that is password protected. All data will be deleted 5 years from when the study has concluded. Confidential data will not be disclosed outside of the study team except as required by law or as allowed by the consent (eg, with the USF institutional review board or those who monitor the study). All data will be deidentified for the analysis. Participants will not receive any compensation for their participation.

## Results

This study was funded in July 2023. We began enrolling participants in December 2024. At the time of writing, 3 participants have been enrolled. It is anticipated that we will conclude this study in December 2025 and expect to disseminate results in March 2026.

## Discussion

### Principal Findings

To our knowledge, this will be the first study to prospectively analyze the impact of a pharmacist-led CGM intervention on glycemia and health behavior in people with T2D in a primary care setting. Our study is unique in that it is not only designed to assess the glycemic benefits of CGM in people with T2D in primary care but also aims to elucidate behavior change resulting from CGM use under a pharmacist-led approach.

We hypothesize that the mean change in HbA_1c_ will be greater for participants enrolled in the intervention cohort as compared to the historical control cohort at 12 weeks. We also hypothesize that participants enrolled in the intervention cohort will experience an improvement in CGM-derived metrics (time in range, mean glucose, time below range, time above range, and glycemic variability) at 12 weeks. For health behavior, we hypothesize that the mean SDSCA score will be higher at 12 weeks compared with baseline. Finally, we hypothesize that an improvement in diet, physical activity, general lifestyle, and medication adherence will be observed on the CGM survey from baseline (second visit) to the end of the study among the intervention group.

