**Inclusion criteria**
Type 2 diabetes.Hemoglobin A_1c_ level of ≥8%.Compatible smartphone with FreeStyle Libre 2 continuous glucose monitoring system.Current use and access to a glucometer for self-monitoring of blood glucose.

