**Exclusion criteria**
Any continuous glucose monitor use within 6 months before study enrollment.Pregnant and planning to become pregnant during the study time frame.History of hypoglycemia requiring third-party assistance.History of diabetic ketoacidosis or hyperosmolar hyperglycemic state within 6 months before study enrollment.Known allergy to medical-grade adhesives.Current use of systemic steroids for any medical condition.Current use of dialysis.

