#### Summary of Diabetes Self-Care Activities

To evaluate change in health behavior we will administer the Summary of Diabetes Self-Care Activities Measure (SDSCA) at baseline and week 12 in the intervention cohort. The within-group difference from baseline to week 12 will be assessed. The SDSCA is a valid and reliable measure of diabetes self-management, which assesses diet, exercise, blood-glucose testing, foot care, and smoking [22]. The strength of the SDSCA includes its brevity and ease of scoring. The SDSCA is a survey scored on an 8-point Likert scale (0-7). Higher scores indicate better compliance with diabetes self-care, whereas a lower score indicates poor self-care performance [22].

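### The health-behavior hypothesis rests on one mean SDSCA score that includes blood-glucose testing, so the planned switch from glucometer to sensor can move it with diet, exercise, foot care and smoking unchanged

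*Protocol article*

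**What the plan says.** The health-behavior hypothesis is in the protocol article's Discussion, under Principal Findings: "we hypothesize that the mean SDSCA score will be higher at 12 weeks compared with baseline". It names one score and no domain.

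The Methods section on the SDSCA says that the instrument "assesses diet, exercise, blood-glucose testing, foot care, and smoking". It gives a scale from 0 to 7 and its direction: "Higher scores indicate better compliance with diabetes self-care, whereas a lower score indicates poor self-care performance". The questionnaire is given at baseline and week 12, in the intervention cohort only, and "The within-group difference from baseline to week 12 will be assessed". The historical cohort serves the primary outcome and has no SDSCA.

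The way glucose is monitored changes between the two administrations by design. The inclusion criteria require "Current use and access to a glucometer for self-monitoring of blood glucose", and the exclusion criteria rule out "Any continuous glucose monitor use within 6 months before study enrollment". The Abstract (Methods) then has participants wear a sensor for 12 weeks.

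The article does not say how a sensor scan counts in the testing domain, and it does not mention analysis by domain. Strengths and Limitations presents the SDSCA as a validated tool and does not mention the overlap with the intervention.

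**The concern.** One of the areas being scored is the activity that the device replaces. A participant who counts a sensor scan as a test may report more testing days at week 12 than at baseline. A participant who counts only fingersticks may report fewer, because the sensor has taken their place. Neither answer says anything about diet, exercise, foot care or smoking.

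A single mean cannot separate this from the wider behavior change that the study says it wants to understand. A rise could be read as broad improvement in self-care when only the testing answers moved. A fall in the testing answers could hide a real gain elsewhere. Without an SDSCA comparator, nothing in the design removes the shift.

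**Working it through.** The article states no SDSCA effect size, SD, significance level or power, so there is no planned figure to reproduce. What follows is an illustration.

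**Inputs from the article.** Scale 0 to 7 and five content areas (section on the SDSCA); n=20 in the intervention cohort (Study Design).

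**Assumptions not in the article.** The score is an equally weighted mean of k domains, with k=5 (k=4 as a check). Only the testing domain changes. The SD of the paired change in the mean score is 1.0 (range 0.75 to 1.5). The test is a two-sided paired t-test at 0.05.

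**Shift in the mean.** If testing goes from b to a, the mean moves by (a − b)/k. With k=5:

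- 3 to 7: (7 − 3)/5 = +0.8
- 5 to 7: (7 − 5)/5 = +0.4
- 7 to 7: 0, because the participant is already at the ceiling
- 3 to 0: (0 − 3)/5 = −0.6

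**Test statistic.** t = shift/(SD/√n). For +0.8: 0.8/(1.0/√20) = 3.58 on 19 df, p about 0.002.

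**Chance of a significant result from the testing domain alone** (noncentral t, n=20, k=5):

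| Testing moves | Shift | SD 0.75 | SD 1.0 | SD 1.5 |
|---|---|---|---|---|
| 3 to 7 | +0.8 | 99% | 92% | 62% |
| 4 to 7 | +0.6 | 92% | 72% | 40% |
| 5 to 7 | +0.4 | 62% | 40% | 21% |
| 6 to 7 | +0.2 | 21% | 14% | 9% |

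The −0.6 shift has the same chances as +0.6, in the unfavorable direction. With k=4 the shifts are larger: 3 to 7 gives +1.0 (99% at SD 1.0) and 5 to 7 gives +0.5 (57% at SD 1.0).

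**Masking.** A shift of −0.6 would exactly cancel a gain of 1.5 points in both diet and exercise, since (1.5 + 1.5)/5 = 0.6.

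**Mixed readings.** If half the participants went from 3 to 7 and half from 3 to 0, the average shift would be (0.8 − 0.6)/2 = +0.1, with extra spread between participants. The mean would then move little, but it would be noisier.

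**After the change proposed below.** With the testing domain outside the mean, its direct contribution to the shift is 0 by construction.

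**The case against.** The strongest reply is that a composite is inferred. Only one sentence in the Discussion speaks of a mean score, and mean may refer to averaging over participants. The Methods list separate content areas, and domain scoring of a secondary questionnaire is often left to the full protocol or analysis plan, which is not shown here. That other document may well settle the scoring. The hypothesis as printed still refers to one score, however, and if scoring by domain is intended, that sentence should say so. The objection here is to a choice that the article states, not to absent detail.

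A reader might go further and infer that the sensor raises the score without any change in self-care, or that it takes the testing domain to its maximum by itself. The article does not support either. It counts glucose testing as self-care, so checking more often is a change in self-care on the instrument's own terms. The CGM survey (Table 2) treats scanning as something that varies between people, with answers starting below once a day. The direction is not fixed, and because current glucometer use is an entry criterion, some participants may start near the ceiling. The SDSCA item wording is not given, so neither way of counting can be assumed.

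Two further replies stand in part. The outcome is secondary, and the Statistical Analyses section is largely descriptive with no formal success criterion, which limits the consequence. Diet and exercise are also covered by the CGM survey and the food and fitness logs. Those are separate sources, though, and do not make the SDSCA score easier to interpret.

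**Conclusion.** The point holds in a limited form. The printed hypothesis uses one score; that score includes glucose testing; the monitoring method changes between the two measurements; and there is no SDSCA comparator. The score can therefore move in either direction with diet, exercise, foot care and smoking unchanged.

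How far it would move cannot be known from the article. Under the assumptions above, the effect of the testing domain alone runs from nothing (already at 7), through +0.4, to +0.8 upward, and to −0.6 downward. All of these figures depend on the assumed weights, baseline level and SD. They show that the effect can be large enough to decide how the result is read, not that it will be. The primary HbA1c comparison is not affected. The change is worth making because it costs little and concerns one of the study's stated objectives.

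**What to change.** - Analyse and report SDSCA change by domain.
- Reword the hypothesis under Principal Findings so that it rests on the domains other than blood-glucose testing.
- Report the testing domain separately and descriptively.
- Give every participant the same instruction on whether a sensor scan counts as a test, and state that instruction in the report. If any week-12 questionnaires were completed without it, say so.
- If the five-domain mean is kept for comparability, report it as supplementary with this caveat.

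The cost is wording and a scoring choice, with the same questionnaire and no new data. The article reports 3 participants enrolled at the time of writing; the choice should in any case be fixed before the SDSCA data are analysed. The downside is several domain results in place of one summary, and less direct comparability with studies that report an overall score.

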### Comparison to Previous Work

Although CGM was first approved for use over 20 years ago, recent technological advancements have made this technology more user-friendly and attainable for a greater number of people living with diabetes, particularly those with T2D. In people with T2D, prospectively driven CGM studies involving pharmacists are currently lacking. In our recent scoping review, we identified only 1 published prospective study evaluating a pharmacist-led CGM service, among a total of 11 published studies in the literature [20,23]. Our methods differ from Fantasia et al [23] in that we are using unblinded CGM devices, which are more commonly used in clinical practice, and are comparing our intervention to a historical cohort managed by a pharmacist in a similar practice setting, rather than to endocrinologists.

In addition, results from our scoping review demonstrated that pharmacist-led CGM was associated with an improvement in glycemic control, with an absolute mean reduction in HbA_1c_ in the literature ranging from –0.4% to –1.8%, which is clinically significant [23-27]. We also found that pharmacist-led CGM was associated with improvements in diabetes self-efficacy [25], improvements in self-care, and improvements in health behavior [28].

### Strengths and Limitations

Several limitations to this study must be mentioned. First, as an observational study design, the lack of randomization may lead to selection bias. For example, it is possible that participants seeking care and who agree to participate in the intervention group might differ in their overall health status and adherence to medical care versus those who do not seek routine medical care. Furthermore, without randomization, differences in baseline characteristics such as medication adherence, lifestyle factors, and socioeconomic status could impact outcomes. Without randomization, it remains difficult to isolate the true effect of the intervention.

In addition, this study may have low external validity, since pharmacist scope of practice varies widely geographically and among health care systems. Further, concerns such as data from a single site and small sample size must also be considered.

On the other hand, several strengths to this study exist, making it a valuable addition to the literature, such as the measurement of clinically significant outcomes (HbA_1c_) as well as the measurement of CGM-derived metrics, which is lacking in many studies. In addition, our study is also using validated measurement tools (ie, SDSCA) to measure health-behavior change. Finally, although observational, the prospective nature of our study establishes a temporal relationship between exposure (to the intervention) and the outcomes, as well as reflecting real-world clinical practice in a primary care setting.

### Future Directions

Our overarching aim is to use the data from this study to support funding to conduct a larger randomized controlled trial that can more rigorously test our hypothesis that pharmacist-led CGM is an intervention that can overcome clinical inertia and improve diabetes-related outcomes in primary care settings.

### Dissemination Plan

The results of this prospective cohort study will be disseminated through presentation in national or international peer-reviewed scientific journals, and at annual meetings of professional conferences.

### Conclusions

There is a need for additional evidence supporting novel approaches to implementing CGM in primary care settings. A prospective cohort study can provide valuable insights into the association of a pharmacist-led approach to implementing CGM.

## Appendix

Multimedia Appendix 1 STROBE (Strengthening the Reporting of Observational studies in Epidemiology) statement and checklist.

Multimedia Appendix 2 Proposal review score sheet for reviewer 1.

Multimedia Appendix 3 Proposal review score sheet for reviewer 2.

Multimedia Appendix 4 Peer-reviewer report from the University of South Florida New Researcher Grant Program.

## Abbreviations

CGM: continuous glucose monitoring
DSMES: diabetes-self management education and support
HbA_1c_: hemoglobin A_1c_
HIPAA: Health Insurance Portability and Accountability Act
REDcap: Research Electronic Data Capture
SDSCA: Summary of Diabetes Self-Care Activities Measure
SMBG: self-monitoring of blood glucose
STROBE: Strengthening the Reporting of Observational studies in Epidemiology
T2D: type 2 diabetes
USF: University of South Florida
